**Fig. 2 Fig2:**
[figure not shown]
Pilot study components. a-eligibility and consent, b-baseline interview, diagnosis and demographics, c-physical measurements (height, weight, body fat percent), d-blood draw, e-Beck Depression Inventory (BDI II), f-Behavioural Activation for Depression Scale (BADS), g-Quality of life scales (SF-12, WSAS, and Q-LES-Q-SF), h-Leisure Motivation Scale (LMS), i-assumptions of risks, j-Physical Activity Readiness Questionnaire (PAR-Q), k- Activity tracking form, l- EQ-5D-5L a standardized instrument to measure health outcomes, m-qualitative individual interviews, n-focus group. S1-behavioural activation for depression, S2-values assessment, S3-goal setting, S4-Breaking it down, S5-avoidance and depression, S6- rumination, S7-ruminations II, S8-relationships, S9-involving others and social skills, S10-asseriveness and communication skills, S11-assetiveness and relaxation strategies, S12-leisure education, S13-problem solving, S14-team building and cooperative games, S15-nutrition and laughter yoga, S16- mindfullness and planning of group outing, S17-understanding sleep, S18-group outing, S19-getting back to work and volunteering, S20-S23 and S25-27 relapse prevention and troubleshooting, S24-booster group/adventure based day trip, S28-booster session and end of study. The qualitative components (l and m) are delivered in the pilot phase only. Adapted from Perera et al. [31]

**Table 1 Tab1:** Pilot study instruments

Instrument	Purpose	Administered	Time to complete (min)	When to complete	Intervention	Control
Baseline questionnaire	Baseline data	Clinician/research assistant	60	Baseline	✓	✓
PAR-Q	Assess readiness for physical activity	Self	10	Baseline	✓	
Assumption of risk form	Inform about risks of attending program	Self	5	Baseline	✓	
BDI-II	Monitor depressive symptoms	Self	5	Baseline	✓	✓
				Weekly	✓	✓
				End of study	✓	✓
SF12, WSAS, Q-LES-Q-SF	Quality of life	Self	10	Baseline	✓	✓
				Session 10	✓	✓
				End of study	✓	✓
BADS	Measure activation and avoidance behaviours	Self	5–10	Baseline	✓	✓
				Weekly	✓	
				End of study	✓	✓
LMS	Measure motivation for engaging in leisure activities	Self and clinician (observational)	15–30	Baseline	✓	✓
				Session 10	✓	
				End of study	✓	✓
EQ-5D-5 L	Health-related quality of life to generate health utility index for calculation of quality-adjusted life years for economic evaluation	Self	5	Baseline	✓	✓
				End of study	✓	✓
Activity-tracking form	To track activity	Clinician and patient	5	Weekly	✓	

### Outcomes

#### Pilot study outcomes

*Primary*:Assess the feasibility of the study process in terms of recruitment, retention, number of sessions completed, average group size and data completion.To assess resources needed including the use of interview rooms, group room, mobile computers to upload activity-tracking data, communication with participants’ clinicians and time investment in the program by the study clinicians.The qualitative component of the pilot study is to assess the need to modify the protocol for the main trial based on the participants’ feedback thus aiming to provide a patient-centred treatment program.

*Secondary*:Assess the change in mood using the Beck Depression Inventory between and within the intervention and control groups.Explore the change in quality of life scores between and within the intervention and control groups.

### Timeline

The pilot study will be conducted over 18 weeks with a total of 30 visits including 28 sessions of behavioural activation in the intervention group and 28 sessions of support group in the control group. Both groups will also receive usual care. The study timeline is presented in more detail as in Fig. 2.

### Sample size

For the feasibility and pilot trial, we will recruit 10 participants in each arm. This number is based on the recommended group therapy size of 6–12 per group session. The pilot data will help to modify the sample size calculation for the main trial.

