The number of studies using BA in a group format is limited to a small number of participants and short follow-up duration. In addition, the majority of patients included in these studies suffered from mild to moderate depressive symptoms in community-based treatment settings. We will test the effectiveness of BA in a representative sample of patients with depression attending a tertiary care hospital setting using a pragmatic study design. The BA intervention will be delivered in a group of 6–12 participants as an adjunct therapy to usual care. Usual care is currently received at the Mood Disorders Program and includes pharmacotherapy, psychotherapy, occupational therapy, case management and regular follow-up visits to the clinic. No structured BA intervention is currently offered at this tertiary mood disorders clinic. While we acknowledge that studies often provide “standard of care,” as the comparator arm, we are reluctant to use this term when defining our own comparator. Contention exists in the medical community over use of the term “standard of care”, which stems largely from the lack of consensus as to (1) what constitutes appropriate use of the term, (2) what expertise is required to declare an intervention to the standard of care, and (3) what level of evidence is adequate to support or refute a therapy as the standard [24]. In fact, researchers suggest that the term not be adopted for any intervention unless confirmatory randomized controlled trials or meta-analyses exist to support this declaration [24]. Recognizing that there is limited evidence to suggest that what is provided to patients in our comparator arm fulfils the criteria for “standard of care,” we have elected to use the term “usual care” to describe the intervention provided for the comparator arm of this trial.

The development of this intervention along with its acceptability among patients with major depressive disorder has been assessed by our team and thoroughly described elsewhere; this work is currently under review [25].

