### The control (The Blues Breakers)

In addition to usual care, the control group will be offered a support group therapy format delivered at the same place, same visit frequency and same duration of program as the intervention group. This support group will be unstructured with no therapist involvement. Participants will be given the group meeting dates and time. Following this, a nurse with specialized training in research (education in data collection) who is not trained in behavioural activation will be present at the group time to collect study-related instruments and check the suicide risk question on the mood scales to ensure participant safety and clinical care. The participants will be asked to choose a topic of discussion, and one participant will lead the discussion. The choice of topic is entirely up to the participants.

We acknowledge that using an active control group has implications for the results of this work. The control group is receiving an enriched “usualcare” whereby patients enter an adjunct support group. Support groups are demonstrated as effective for improving quality of life [26], and thus, the implications of an active control arm will require consideration in the discussion and interpretation of findings for this pilot trial. This support group is intended to simulate the intervention group format to minimize risk of a biased estimate of BA effectiveness by reducing the potential placebo effect [27] which may result from frequent clinic visits and having additional attention beyond usual care.

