### Statistical analyses

Data generated from the pilot study will help inform the main trial by testing the study procedures. Therefore, no formal statistical analyses will be performed for the pilot data. Description of the study participants and simple tabulation of the pilot data will be presented. Data exploration will be performed to compare the mean difference (and 95 % confidence intervals) of the BDI-II and quality of life scores between intervention and comparator groups at the end of the trial using *t* test and within groups for repeated measures using analysis of variance (ANOVA). All randomized participants will be included in the analyses. The statistical analyses of the pilot data will be exploratory only as the sample size will not allow for definitive analyses. We will use Stata version 12 software for analyses.

Summary of the study objectives and proposed statistical analyses are presented in Table 2. We will consider the following criteria to deem the study is feasible to be conducted:At least 20 % of potential participants agree and enrol in the study (given the time commitment of 18 weeks and frequency of face-to-face visits we would expect fewer participants to enrol)Completion rate of 80 %, that is to say, we will have final visit data on at least 80 % of the participantsWe expect 80 % completion of weekly measurement scales

**Table 2 Tab2:** Summary of the study objectives, outcomes and analysis plans

Aim	Objectives	Outcome	Hypothesis	Statistical analysis
Primary	Assess feasibility of recruitment, retention, group size and data completion	Recruitment and retention rates, data missingness	BA is feasible and acceptable	Descriptive statistics: mean and SD for continuous variables and proportions for dichotomous variables
	Assess resources needed	Group and interview rooms needed, number of clinicians to deliver groups, average length of group session (time needed per session)		Descriptive statistics: mean and SD for continuous variables and proportions for dichotomous variables
	Participants’ feedback and personal experiences	Qualitative study feedback		Qualitative study results based on grounded theory
Secondary	Clinical outcomes: BDI-II and quality of life	Rate of completion of the scales	The intervention group will show improvement in these scales	Between and within group comparisons of the BDI-II and quality of life scales

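### With one therapy group per arm, the exploratory t-test 95% CI ignores group effects, and the pilot cannot estimate the ICC

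*Protocol article*

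**What the plan says.** - **Sample size:** "we will recruit 10 participants in each arm". The reason given is "This number is based on the recommended group therapy size of 6–12 per group session", and the section ends with "The pilot data will help to modify the sample size calculation for the main trial".
- **Definition of behavioural activation:** "The BA intervention will be delivered in a group of 6–12 participants as an adjunct therapy to usual care".
- **The control (The Blues Breakers):** "the control group will be offered a support group therapy format delivered at the same place, same visit frequency and same duration of program". This group is unstructured and led by its own members.
- **Timeline:** "The pilot study will be conducted over 18 weeks with a total of 30 visits", made up of "28 sessions of behavioural activation in the intervention group and 28 sessions of support group in the control group".
- **Allocation and randomization:** patients are randomised individually, 1:1.
- **Statistical analyses:** "Data exploration will be performed to compare the mean difference" in BDI-II and quality-of-life scores at the end of the trial, with a 95% confidence interval from a t test. The section calls the analysis exploratory because the sample is small. It names no term for therapy group.

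The article nowhere mentions clustering, an ICC or a design effect.

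**The concern.** Patients are randomised individually but treated in groups. Members of the behavioural activation (BA) group share therapists, outings, social-skills work and one another over 28 sessions. Members of the support group choose their own topics, so what that arm receives depends on who is in it. Outcomes within a group may therefore be correlated. A two-sample t test assumes that they are not.

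Two things are at stake. First, the planned interval is presented as a 95% interval for BA versus support, but as an interval for that contrast it covers less often than 95%. Second, the pilot is meant to feed the main trial's sample size, and it holds no information on the between-group variance that a group-delivered trial needs.

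**Working it through.** **Step 1. How many groups per arm?** The article does not state the number, but its figures settle it.
- Two groups of at least 6 need 12 people, and an arm has 10. One group of 10 lies within 6–12.
- The abstract's schedule is twice weekly for 10 weeks, then weekly for 8: 2×10 + 8 = 28 sessions in 18 weeks. That equals the whole pilot, so there is no second wave.

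The 10 per arm has no power calculation behind it, so there is no statistical figure to reproduce.

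**Step 2. Can the group effect be estimated?** With g groups per arm, the between-group variance has 2(g−1) degrees of freedom. For g = 1 this is 0. No analysis plan can recover it from these data.

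**Step 3. What does the t interval miss?** Let σ² be the total variance, m the number per group and ICC the intraclass correlation, equal in both arms.
- True variance of the difference in means: (2σ²/m)·[1+(m−1)ICC].
- Expected variance as the t test estimates it: (2σ²/m)·(1−ICC).
- Ratio of true to t-test SE: R = √{[1+(m−1)ICC]/(1−ICC)}.
- Actual coverage: P(|T| < t₀.₉₇₅/R) on 2m−2 df.

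At m = 10 there are 18 df and t₀.₉₇₅ = 2.101. The planned half-width is 2.101×√(2/10) = 0.94 pilot SDs. The ICC values are assumptions.

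| ICC | 1+9·ICC | R | Coverage, m = 10 | Coverage, m = 8 |
|---|---|---|---|---|
| 0.01 | 1.09 | 1.05 | 93.9% | 94.2% |
| 0.02 | 1.18 | 1.10 | 92.8% | 93.3% |
| 0.05 | 1.45 | 1.24 | 89.4% | 90.6% |
| 0.10 | 1.90 | 1.45 | 83.5% | 85.9% |

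Example at ICC 0.05: R = √(1.45/0.95) = 1.235. The m = 8 column corresponds to the 80% final-visit criterion. Simulation with 200,000 runs gave 94.0%, 89.4% and 83.4% at ICC 0.01, 0.05 and 0.10 (m = 10).

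**Step 4. If only the BA arm clusters.** Then R = √{(2+9·ICC)/(2−ICC)} at m = 10. Coverage is 94.5%, 92.3% and 89.4% at ICC 0.01, 0.05 and 0.10.

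**Step 5. Use of the pilot SD in the main trial.** The pooled pilot variance estimates σ²(1−ICC), that is 98%, 95% and 90% of σ² at ICC 0.02, 0.05 and 0.10. A sample size built on it therefore needs the multiplier [1+(m−1)ICC]/(1−ICC). At m = 10:
- ICC 0.02: 1.18/0.98 = 1.20
- ICC 0.05: 1.45/0.95 = 1.53
- ICC 0.10: 1.90/0.90 = 2.11

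The usual 1+(m−1)ICC is right only when the SD entered is the total SD.

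Illustration, assuming a difference of 0.5 total SDs, 80% power and two-sided 0.05: 63 per arm without clustering. With groups of 10 this becomes 63×1.45 = 91.4, rounded up to 92, at ICC 0.05, and 63×1.90 = 119.7, rounded up to 120, at ICC 0.10.

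**The case against.** The strongest reply is that this is a feasibility pilot. The Background says such trials are not for testing effectiveness, and Statistical analyses disclaims formal analysis. The three feasibility criteria (20% enrolment, 80% final-visit data, 80% completion of weekly scales) use neither the interval nor the SD, so correcting the interval changes no stated decision. That stands, and it limits the severity. It does not remove the error: the article's caveat is about sample size, and adding members to the same two groups would leave group confounded with arm.

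A second reply is that the size of the problem rests on an ICC that the documents do not give. This also stands. At ICC 0.01 the loss is about one percentage point, and the unstructured control may cluster less than BA (Step 4).

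A third reply is that a separate analysis plan may handle clustering. It could widen the interval using an outside ICC, but it could not estimate the ICC from one group per arm. The t test is named in the article itself.

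A reader might also infer that the main trial will be undersized. The documents do not support that. Sample size says only that pilot data will help to modify the calculation. It does not say that the pilot SD will be the input or that clustering will be ignored, and the main-trial calculation is not shown.

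**Conclusion.** The point holds at moderate severity. The article's figures imply one therapy group per arm, so the between-group variance and the ICC cannot be estimated. The between-arm 95% interval is too narrow for any positive ICC. If both arms cluster equally with 10 analysed per group, coverage runs from about 94% at ICC 0.01 to about 83% at ICC 0.10. If only the BA arm clusters, it is about 92% at ICC 0.05 and 89% at 0.10. All of these rest on assumed ICCs.

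It would be too strong to conclude that the pilot cannot supply any of the variance the main trial needs. That is exact only for the between-group part. The pilot can still give a rough within-group SD, as well as recruitment, retention and group size, and group size is itself an input to the design effect.

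**What to change.** 1. **Statistical analyses.** State that the between-arm interval is conditional on the two groups observed and makes no allowance for group effects. Beside it, report intervals with the SE multiplied by √{[1+(m−1)ICC]/(1−ICC)} over a stated range of assumed ICCs, with m the number analysed per group. At m = 10 the multipliers are 1.10, 1.24 and 1.45 for ICC 0.02, 0.05 and 0.10.
2. **Sample size.** State that the pilot cannot estimate the ICC. State also that any main-trial sample size based on the pilot's within-group SD will be multiplied by [1+(m−1)ICC]/(1−ICC), with an externally justified ICC and m the group size expected in the main trial. At m = 10 this is about 1.20, 1.53 and 2.11 for the same ICCs.

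The cost is some wording and a short table. The exploratory interval becomes wider and the planned main trial larger. No extra pilot participants are needed.

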### Recruitment

Patients with a diagnosis of depressive disorders referred to the mood disorders clinic will be approached for participation in the study. Consecutive patients attending the clinic will be asked if they are interested in participating in the study. Following initial screening for eligibility, patients will be asked to provide written informed consent prior to any study-related procedures. Potential participants will be approached through clinicians with direct clinical contact with potential participants. A simple log will be kept to track the number of individuals approached, number declined, and number excluded and reasons for exclusion.

### Allocation and randomization

We will employ a parallel group design to test the feasibility of behavioural activation study in depression. Eligible and consenting patients will be randomly allocated to the intervention or control arms using a 1:1 allocation ratio. Allocations will be randomly assigned using a block randomization system of block sizes of 2, 4 and 6.

### Blinding and concealment of randomization

This pilot trial is an open label trial as blinding is not possible for participants (behavioural activation intervention) or the clinician administering the intervention. However, a research assistant not involved in the intervention or the control condition will allocate the participants based on the randomization system provided. The clinicians referring participants, the participants at the time of enrolment (signed consent and baseline visit completed) and the clinicians providing the BA intervention or the control groups will have no knowledge of the allocation prior to the start of the first intervention or control groups. Following the consent and baseline assessment, participants will be informed what group they will be attending. The clinicians will receive a list of the participants to attend their respective groups. Allocation concealment will be ensured by assigning study ID numbers to all participants at the time of enrolment and before randomization. The allocation then occurs as above using the assigned ID numbers with no other identifiers; these IDs will then be placed in an opaque envelope and randomly picked from the envelope and allocated to the intervention or control based on the block randomization system. Following the completion of the random allocation process, the ID numbers will then be identified by name, and the participants will be informed of their assigned groups. Further allocation concealment will occur at the data analysis level where data analyst will be blinded to the allocation. The clinical outcomes measures are self-administered, and therefore, the participants cannot be blinded to their allocation group.

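### Blocks of 2, 4 and 6 applied to IDs in random order limit the arm-size split but balance no patient characteristic, although baseline BDI-II could be used to restrict the draw cheaply

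*Protocol article*

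**What the plan says.** All references are to the protocol article.

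- **Sample size:** "we will recruit 10 participants in each arm". The reason given is practical: "This number is based on the recommended group therapy size of 6–12 per group session".
- **Allocation and randomization:** patients are "randomly allocated to the intervention or control arms using a 1:1 allocation ratio", with a "block randomization system of block sizes of 2, 4 and 6". No stratification factor is named, and neither the order nor the number of blocks is given.
- **Blinding and concealment of randomization:** concealment rests on "assigning study ID numbers to all participants at the time of enrolment and before randomization". The section glosses enrolment as consent signed and baseline visit done: "the participants at the time of enrolment (signed consent and baseline visit completed". The IDs carry no other information, go into an opaque envelope, and are "randomly picked from the envelope and allocated to the intervention or control based on the block randomization system". Names come last: "Following the completion of the random allocation process, the ID numbers will then be identified by name". This describes one batch draw after baseline, not allocation patient by patient as people arrive.
- **Table 1** lists the BDI-II at baseline in both arms.
- **Statistical analyses** plans an end-of-trial comparison of BDI-II by t test with a 95% interval, names no baseline adjustment, and calls the analysis exploratory.

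**The concern.** Permuted blocks do two things. They hold the arm sizes close together, and they balance the arms along the order in which patients meet the list, usually calendar time. Here that order is a random draw, so the second function is lost: adjacent IDs share neither an enrolment period nor a level of severity. What remains is control of arm size.

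A batch draw after baseline is also the situation in which balancing on a measured covariate is easiest, because the whole sample is known before anyone is allocated. The article itself describes the BDI-II as strongly predictive of patient-important outcomes (Data collection methods), yet the draw makes no use of it. With 10 per arm, a sizeable chance gap in baseline severity is likely enough to matter when the end-of-trial BDI-II difference is read, and the planned t test would carry that gap straight into the estimate.

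**Working it through.** **Inputs.** n = 20, 10 per arm (Sample size); blocks of 2, 4 and 6 (Allocation and randomization); IDs in random order (Blinding and concealment of randomization). The article gives no BDI-II standard deviation and no baseline-outcome correlation. Results are therefore in SD units, baseline is taken as normal, and the correlation r is an assumption with range 0.3 to 0.7. The 10 per arm comes from therapy-group size, so there is no power calculation to reproduce.

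**1. Arm size.** All blocks and the total are even. If the last block is unfinished, 2 or 4 of its places have been used, and either leaves a difference of 0 or 2 between the arms. The worst split is 11:9. Simple randomisation would be worse than 11:9 with probability 50.3%, so the blocks do useful work here.

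Whether 10:10 is certain depends on the unstated block order:

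| Block order | P(10:10) |
|---|---|
| Sizes drawn with equal probability (assumed) | 81.0% |
| Fixed cycle 2-6-4 or 6-2-4 (closes at 20) | 100% |
| Fixed cycle 2-4-6, 4-2-6 or 4-6-2 | 60% |
| Fixed cycle 6-4-2 | 67% |

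**2. Baseline balance under the planned draw.** With IDs in random order, the between-arm difference in mean baseline BDI-II has SD √(1/10 + 1/10) = √0.2 = 0.447. The chance of a gap above 0.5 SD is 2 × [1 − Φ(0.5/0.447)] = 2 × [1 − Φ(1.118)] = 26%. Simulation of the 2/4/6 blocks on a random draw (40,000 trials) gives SD 0.447 and 26%. An unblocked 10:10 shuffle gives 0.449 and 26%. For baseline balance the blocks add nothing.

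**3. Baseline balance under the alternatives (simulation, n = 20).**

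| Allocation | P(gap > 0.5 SD) | 10:10 assured | Mean variance factor, adjusted analysis |
|---|---|---|---|
| Planned draw | 26% | depends on block order | 1.065 |
| 5:5 within each BDI-II half | 7% | yes | 1.021 |
| Ordered by BDI-II, 2/4/6 blocks totalling 20 | 0.4% | yes | 1.007 |
| Ordered by BDI-II, 2/4/6 blocks not constrained to 20 | 2.5% | no (81%) | not computed |

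The variance factor is the variance of the baseline-adjusted difference relative to perfect baseline balance.

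**4. Precision of the end-of-trial difference (outcome SD units).** The unadjusted standard error is √0.2 = 0.447. Adjusted, it is about √[0.2 × (1 − r²) × factor].

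- r = 0.5, adjustment alone: √(0.2 × 0.75 × 1.065) = 0.400.
- r = 0.5, adjustment plus ordering: √(0.2 × 0.75 × 1.007) = 0.389. With halves: √(0.2 × 0.75 × 1.021) = 0.391.
- r = 0.3: 0.440 from adjustment alone, 0.428 with ordering.
- r = 0.7: 0.330 from adjustment alone, 0.320 with ordering.

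At r = 0.5 adjustment supplies about 0.048 of the total gain of 0.058. At r = 0.7 the pattern is the same. At r = 0.3 the total gain is only about 0.02, and the restriction supplies more than half of it.

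**The case against.** The strongest reply is that nothing here is an error. The draw is concealed and unbiased; the section on allocation promises 1:1 and no covariate balance; and every unstratified trial leaves measured covariates to chance. All that the random order removes is balance over enrolment time, and no time trend is identified in this single-site sample of 20. The clinical comparison is exploratory, and at r of 0.5 or more adjustment supplies most of the precision. All of this stands, and it makes the point an optional improvement.

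Three stronger readings are tempting, and the document does not support them.

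- **That the blocks are useless.** They cap the split at 11:9, and both 9 and 11 lie within the stated group size of 6 to 12.
- **That the plan contradicts its own 10 per arm.** The 19% chance of 11:9 assumes equally likely block sizes. The block order is not stated, a condensed article may leave it to the full protocol, and some orders close exactly at 20.
- **That a severity gap would damage the primary feasibility outcomes.** The feasibility criteria are enrolment of at least 20%, final-visit data on 80% and 80% completion of weekly scales. None is framed by arm, and recruitment precedes allocation. No passage or figure links a chance gap between arms to attendance or drop-out.

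The change is also not free: concealment now relies on IDs with nothing beside them. And that the BDI-II is completed before the draw is a well-supported inference, not an explicit statement. Two forms that Table 1 lists at baseline are for the intervention arm only, so not every baseline form clearly precedes allocation.

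**Conclusion.** The point holds as a low-consequence missed opportunity. As described, the blocking controls arm size and nothing else, and leaves about a 26% chance of a baseline BDI-II gap above 0.5 SD, where a simple restriction would leave 7% or 0.4%. What is at stake is chance imbalance and some precision in the exploratory BDI-II comparison; validity is not in question.

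The percentages assume 20 patients and a roughly normal baseline. The precision figures depend on the assumed correlation. Both rest on reading the envelope procedure as a single batch draw after baseline, which the text supports.

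**What to change.** 1. **Allocation and randomization; Blinding and concealment of randomization.** After all baseline visits, have the research assistant who allocates do one of the following:
   - randomise 1:1 within the lower and upper halves of baseline BDI-II; or
   - list the anonymous IDs in order of baseline BDI-II and apply a random sequence of blocks of 2, 4 and 6 constrained to total the number enrolled. The constraint is needed: ordering alone gives 2.5% and does not assure 10:10.
2. **Procedure.** State that the BDI-II is completed before the draw.
3. **Statistical analyses.** Replace the unadjusted end-of-trial t test for BDI-II with a between-arm difference adjusted for baseline BDI-II, reported with its 95% interval. Without this, the improved balance would not show as a narrower interval; the t test would be somewhat conservative.

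**Cost.** A few sentences and no new data. A score stands beside each ID at allocation, so names should stay unlinked until allocation is complete, as now planned. The analysis must reflect the restriction.
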